### Endpoints

2.2.

The aims of this case–control study are to identify the diagnostic immune cells biomarker(s) of heatstroke and prognostic immune cells biomarker(s) of heatstroke within 30 days.

For exploring diagnostic biomarker(s) that distinguishes patients with heatstroke from patients with sepsis, patients with aseptic inflammation and healthy individuals, because this trial is a case–control study, no endpoints can be provided.

For exploring prognostic biomarker(s) for patients with heatstroke, the primary endpoint is all-cause mortality within 30 days. The secondary endpoints include incidence of the organ injury events within 30 days, including neurological dysfunction, acute heart failure, acute renal failure, or respiratory failure, which are diagnosed as following:

Neurological dysfunction will include stroke, which will be diagnosed based on symptoms of unconsciousness or focal neurologic deficit and the results of computerized tomography and magnetic resonance imaging; and delirium, which will be diagnosed as described (22).

Acute heart failure will be diagnosed according to symptoms of breathlessness, tiredness, and fatigue; clinical signs; abnormalities of electrocardiogram(ECG) such as atrial fibrillation, Q waves, left ventricle hypertrophy, and a widened QRS complex (23); left ventricular ejection fraction (LVEF) ≤ 40% based on the results of echocardiography (23); and elevated levels of B-type natriuretic peptide (BNP) or NT-proBNP (24).

Acute renal failure will be defined as stage 3 acute kidney injury according to the KDIGO criteria (25): stage3: creatinine level in serum ≥4.0 mg/dL (353.60 μmol/L) or ≥ 3 times baseline within 7 days, or requirement for renal replacement therapy, or urine output <0.3 mL/kg/h for ≥24 h OR anuria for ≥12 h.

Respiratory failure will be defined as pH < 7.35 and PaCO_2_ > 45 mmHg or as PaO_2_/FiO_2_ < 200 based on invasive or non-invasive ventilation or arterial blood gas analysis (26, 27) within 30 days. If patients with concomitant pulmonary diseases prior to admission meet above diagnostic criteria, the patient will not be considered to have lung injury caused by heatstroke and will be excluded.

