#### Inclusion and exclusion criteria

2.1.1.

Participants will be recruited from the International Medical Center and from the Departments of Emergency Medicine and of Anesthesiology at West China Hospital of Sichuan University. Four cohorts of 40 individuals each will be recruited: heatstroke patients, sepsis patients, patients undergoing CPB, and healthy controls. The inclusion and exclusion criteria for each cohort are shown in Table 1. Participant recruitment and data collection will begin on January 1, 2023 and will continue until October 31, 2023.

**Table 1 tab1:** Inclusion and exclusion criteria for subject enrollment.

Subjects	Inclusion criteria	Exclusion criteria
Heatstroke patients	(1) Age ≥ 18 years	(1) Pregnant women.
	(2) History of exposure to extreme environmental heat or vigorous muscle exertion	
	(3) Core body temperature > 40°C or symptoms of central nervous system (CNS) dysfunction, such as coma, delirium, or convulsions	(2) Comorbid with immune system disease within the 6 months prior to admission, including but not limited to acquired immune deficiency syndrome (AIDS), multiple myeloma, rheumatoid arthritis, systemic lupus erythematosus, multiple sclerosis, myasthenia gravis, scleroderma, Crohn’s disease, and ulcerative colitis.
	(4) Written informed consent to participate	
Sepsis patients	(1) Age ≥ 18 years	(3) Comorbid with malignant tumor and hematological diseases.
	(2) Suspected or known infection	
	(3) Sequential organ failure assessment (SOFA) score ≥ 2	
	(4) Written informed consent to participate	(4) History of organ or bone marrow transplantation.
Patients undergoing CPB	(1) Age ≥ 18 years	
	(2) Valve replacement or coronary artery bypass under cardiopulmonary bypass	
	(3) Written informed consent to participate	
Healthy controls	(1) Age ≥ 18 years	(5) History of immunosuppressive therapy, including glucocorticoids, soluble microbial products (SMSs), polyclonal and monoclonal antibodies, antimetabolite and alkylating agents, or radiotherapy within the 6 months prior to admission.
	(2) Body mass index 18–24 kg/m^2^	
	(3) Health examination within the previous 6 months indicated no abnormality	
	(4) Written informed consent to participate	

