Additional information will be recorded onto case report forms for the three patient cohorts. In the case of heatstroke and sepsis patients, the location of onset, symptoms, and vital signs on admission will be collected. In the case of CPB patients, preoperative data will be recorded on surgical diagnosis, New York Heart Association cardiac function classification, and EuroSCORE II, as will intraoperative data about surgical procedure, surgery time, anesthesia time, amount of blood transfusion, urine output, and medicines used during surgery. We will record mechanical ventilation, renal replacement therapy, and transfusion, as well as use of vasoactive agents, glucocorticoids, and antibiotics during hospitalization for the three patient cohorts. These groups will be followed up at 30 days after admission, either in person if the individual remains in hospital or by telephone or WeChat if the individual has been discharged. During follow-up, data will be collected on death, infection, and complications affecting cardiovascular, respiratory, nervous, digestive, or urinary systems.

These data will be entered onto case report forms. To protect confidentiality, the files will be stored in a secure and locked place and manner, and the subject identification and private information will be deleted from all study documents. To control the quality of data, supervising investigators will be required to ensure the accuracy and completeness of the data. Then the data will be doubly entered into the EpiData 3.10 database system by two investigators. After finishing the data entry and dealing with the query, the database will be locked under the orders of the principal investigator. No one is allowed to view the database without authorization; otherwise, they should notify the principal investigator.

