#### Blood collection

2.4.1.

Venous blood (10 mL) will be collected into tubes coated with ethylenediamine tetraacetic acid within 24 h after admission in the case of heatstroke and sepsis patients, at the end of CPB in the case of CPB patients, and during outpatient visits at the International Medical Center in the case of healthy controls.

Within 4 h after collection, 8 mL of the blood samples will be processed to isolate peripheral blood mononuclear cells (PBMCs; see section 2.4.2), while the remaining 2 mL of blood will be centrifuged at 100 *g* at 4°C for 5 min, and then 500 μL of plasma will be stored at −80°C for cytokine assays (see section 2.4.5).

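### For heatstroke patients who present with delirium, the 30-day neurological secondary endpoint is already met when the blood marker is measured

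*Protocol article*

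**What the plan says.** All references are to the protocol article.

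- **Entry (section 2.1.1, Table 1).** The third heatstroke criterion is "Core body temperature > 40°C or symptoms of central nervous system (CNS) dysfunction, such as coma, delirium, or convulsions". Delirium is a named example within an either/or criterion, so it can satisfy the criterion but is not required.
- **Outcome (section 2.2).** "The secondary endpoints include incidence of the organ injury events within 30 days, including neurological dysfunction". Neurological dysfunction is then defined as stroke, with imaging, "and delirium, which will be diagnosed as described (22". No condition on the time of onset is attached. For prognosis, "the primary endpoint is all-cause mortality within 30 days".
- **Marker (section 2.4.1).** Blood is taken "within 24 h after admission in the case of heatstroke and sepsis patients".
- **Follow-up (section 2.4).** "These groups will be followed up at 30 days after admission". For heatstroke and sepsis patients "the location of onset, symptoms, and vital signs on admission will be collected", but section 2.2 does not use these data to separate existing from new events.
- **Analysis (section 2.5).** Immune cell subsets are compared by outcome with a t-test or Mann–Whitney test. ROC curves follow, with a threshold that maximises the Youden index, and then sensitivity, specificity, predictive values and likelihood ratios.

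**The concern.** A prognostic marker has to be measured before the event it predicts. Here the same sign can bring a patient into the heatstroke cohort and be counted as that patient's outcome, and the outcome window opens before the sample is taken. For such patients, an association between an immune subset and neurological dysfunction is cross-sectional: the marker describes a state that is already visible at the bedside.

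Identifying prognostic biomarkers is one of the study's two stated aims. A subset that only reflects delirium on arrival could be reported as predicting neurological outcome, with a threshold and a sensitivity and specificity that would not hold for patients in whom the outcome is still open.

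**Working it through.** **Step 1: the definitions side by side.** The article has no figure to reproduce: section 2.3 states that no sample size was calculated, and no event rates are given. The check is first one of definitions and timing.

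- Is delirium possible at entry? Yes (Table 1).
- Does delirium count as an outcome? Yes (section 2.2).
- Can the outcome window include time before the draw? Yes: follow-up is timed from admission (section 2.4), and the draw may come up to 24 h later (section 2.4.1).
- Is there a rule for conditions already present? Only one, for respiratory failure in patients with pulmonary disease before admission (section 2.2). There is none for delirium.

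Read as written, delirium present on arrival, or starting between arrival and the draw, is a counted event.

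**Step 2: how much this could matter.** The inputs below are assumptions, except N.

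- N = 40 heatstroke patients (sections 2.1.1 and 2.3).
- q = share with delirium at entry, 0.10 to 0.75.
- r = rate of new neurological events among the rest, 0.10 to 0.30.
- a = 0.80, the AUC of a marker for delirium at entry. The same marker has AUC 0.50 for new events, so it has no prognostic value.

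Formulas:

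- Counted events = N × [q + (1 − q) × r].
- Share of counted events already present: s = q / [q + (1 − q) × r].
- Apparent AUC = s × a + (1 − s) × 0.50.

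Lowest case, q = 0.10 and r = 0.30: s = 0.10 / (0.10 + 0.27) = 0.27, and the AUC is 0.27 × 0.80 + 0.73 × 0.50 = 0.58. Highest case, q = 0.75 and r = 0.10: s = 0.75 / (0.75 + 0.025) = 0.97, and the AUC is 0.97 × 0.80 + 0.03 × 0.50 = 0.79.

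In the table, the first value in each range is for r = 0.10 and the second for r = 0.30.

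| q | Delirious at entry | Free of delirium at entry | New events | Counted as written | Share already present | Apparent AUC |
|---|---|---|---|---|---|---|
| 0.10 | 4 | 36 | 3.6 to 10.8 | 7.6 to 14.8 | 53% to 27% | 0.66 to 0.58 |
| 0.25 | 10 | 30 | 3 to 9 | 13 to 19 | 77% to 53% | 0.73 to 0.66 |
| 0.50 | 20 | 20 | 2 to 6 | 22 to 26 | 91% to 77% | 0.77 to 0.73 |
| 0.75 | 30 | 10 | 1 to 3 | 31 to 33 | 97% to 91% | 0.79 to 0.77 |

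Over the same grid, a = 0.70 gives an apparent AUC of 0.55 to 0.69, and a = 0.90 gives 0.61 to 0.89. The value for truly new events is 0.50 throughout.

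**The case against.** The strongest reply has four parts.

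1. **The word incidence in section 2.2 already implies new events.** It points that way, but no onset rule makes it operational and follow-up is timed from admission. The delirium reference is not at hand; the article cites it for how delirium is diagnosed, not for when it began.

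2. **A condensed article may leave onset rules to the full protocol or analysis plan.** This carries weight for renal, cardiac and respiratory failure, which are not entry criteria and share only the timing gap. It carries less for delirium, where two definitions printed in the article overlap.

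3. **Admission symptoms and 30-day complications are recorded separately, so an analyst could separate them.** That is true, and it makes the repair cheap. But the endpoint as defined does not ask for it.

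4. **The study is exploratory and the endpoint is secondary.** This limits the severity. It does not make an existing state a predicted one.

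Several stronger readings are tempting, and the article does not support them:

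- A reader might infer that most heatstroke patients meet the endpoint at entry. No share is given, a core temperature above 40°C is an alternative route, and coma and convulsions, the other two examples, are not themselves components of the endpoint.
- A reader might infer that chronic dialysis would count as a predicted renal event. The endpoint is acute renal failure, defined as stage 3 acute kidney injury.
- A reader might infer that being ventilated is itself an event. Respiratory failure is defined by blood gas values; ventilation is only part of how it is assessed.
- A reader might infer that the whole prognostic aim fails. Mortality cannot be present at sampling.

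**Conclusion.** The point holds for one component, delirium, of one of the four secondary organ-injury endpoints. For patients who present with delirium, the neurological endpoint is met before or at the time of sampling, and the section 2.5 results for it would blend cross-sectional association with prediction.

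The size depends on a share that the article does not report. Under the stated assumptions, a marker with no prognostic value would show an apparent AUC of about 0.58 to 0.79, and 27% to 97% of counted neurological events would already be present at entry. These figures illustrate the mechanism and do not estimate what this study will find.

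Acute renal, cardiac or respiratory failure already present at the draw has the same timing gap, without the overlap with entry. Thirty-day mortality and the diagnostic comparison are not affected. Severity: should be fixed, but not a flaw that undermines the study.

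**What to change.** In section 2.2:

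- Count as prognostic organ-injury events only those with onset after the blood sample.
- Record the date and time of onset for each event. The case report form needs this field from the start, because discharged patients are reached by telephone or WeChat and onset is hard to reconstruct at day 30.
- For each organ endpoint, analyse the patients free of that condition at sampling, using the admission symptoms and laboratory results already collected.
- Report delirium present at sampling as a baseline characteristic. Its persistence can be at most a separate descriptive outcome, with deaths before assessment shown alongside. It should not replace the endpoint, because persistence can occur only in patients whom the risk set excludes.

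The cost is a few sentences, one field per event, and fewer events. Under the assumptions above, about 1 to 11 new neurological events would remain among 40 patients (2 to 6 if half are delirious at entry). That is too few for a stable ROC threshold, so the neurological analysis should be labelled descriptive.

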### Study protocol

2.4.

Specially trained investigators will screen individuals for potential inclusion based on the inclusion and exclusion criteria, and they will obtain written informed consent from the individuals or their legal representatives. The items to be measured are listed in Table 2. The following baseline data will be recorded from all participants on case report forms: age, sex, ethnicity, profession, education level, body mass index, history of smoking and drinking, family medical history, laboratory results, comorbidities, and treatments. Comorbidities include cardiovascular disease, hypertension, asthma, chronic obstructive pulmonary disease, epilepsy, stroke, diabetes, hyperthyroidism, hypothyroidism, chronic liver disease, virus infection, and neurological disease. Treatments include antihypertensive agents, aspirin, statins, anticoagulant drug, oral antidiabetic agents, insulin, and levothyroxine.

**Table 2 tab2:** Schedule of enrollment, intervention, and assessment.

Items	Screening	Post-allocation	1 month after trial
	Visit1 (Within 24 h of admission)	Visit2 (During hospitalization)	Visit3
Informed consent	**×**		
Inclusion/exclusion criteria	**×**		
Basic information^a^	**×**		
Smoking and drinking history	**×**		
Family medical history	**×**		
Comorbidities and treatments^b^	**×**		
The location of onset, symptoms and vital signs on admission (for heatstroke patients and sepsis patients)	**×**		
Preoperative data (for CPB patients)		**×**	
Intraoperative data (for CPB patients)		**×**	
Mechanical ventilation		**×**	
Renal replacement therapy		**×**	
Transfusion		**×**	
Usage of medication^c^		**×**	
Death			**×**
Infection			**×**
Complications^d^			**×**

a Age, gender, job, height, and weight, etc.

b Comorbidities include cardiovascular disease, hypertension, asthma, chronic obstructive pulmonary disease, epilepsy, stroke, diabetes, hyperthyroidism, hypothyroidism, chronic liver disease, virus infection, and neurological disease. Treatments include antihypertensive agents, aspirin, statins, anticoagulant drug, oral antidiabetic agents, insulin, and euthyrox.

c Including vasoactive agents, glucocorticoids, and antibiotics.

d Including cardiovascular, respiratory, nervous, digestive or urinary systems complications.

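### The renal and heart-failure endpoints have no rule for pre-existing disease, unlike the lung endpoint, so chronic disease can be counted as heatstroke organ injury

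*Protocol article*

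**What the plan says.** In section 2.2 (Endpoints) the primary prognostic endpoint for heatstroke patients is 30-day mortality. Organ injury comes second: "The secondary endpoints include incidence of the organ injury events within 30 days".

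- **Kidney.** "Acute renal failure will be defined as stage 3 acute kidney injury according to the KDIGO criteria". The criteria then listed are "creatinine level in serum ≥4.0 mg/dL (353.60 μmol/L) or ≥ 3 times baseline within 7 days, or requirement for renal replacement therapy", followed by urine-output alternatives. They are joined by *or*.
- **Heart.** Acute heart failure is diagnosed from symptoms, clinical signs, ECG abnormalities, "left ventricular ejection fraction (LVEF) ≤ 40% based on the results of echocardiography" "and elevated levels of B-type natriuretic peptide (BNP) or NT-proBNP". These items are joined by *and*. None carries an onset or change requirement.
- **Lung.** Respiratory failure alone has a rule for earlier disease. It begins "If patients with concomitant pulmonary diseases prior to admission meet above diagnostic criteria", and goes on to say that such patients are not regarded as having heatstroke lung injury and are excluded.

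The exclusion criteria in Table 1 cover pregnancy, immune disease, malignancy and blood disease, transplantation and immunosuppressive therapy. They do not mention chronic kidney disease, dialysis or chronic heart failure. Section 2.4 names the comorbidities to be recorded: "Comorbidities include cardiovascular disease, hypertension, asthma, chronic obstructive pulmonary disease, epilepsy, stroke, diabetes, hyperthyroidism, hypothyroidism, chronic liver disease, virus infection, and neurological disease". Note b to Table 2 repeats that list. Baseline laboratory results are also recorded, without naming the analytes, and renal replacement is recorded during the hospital stay.

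**The concern.** The endpoints are meant to capture injury that is acute and that heatstroke caused; the lung rule shows that intent. Two of the written renal routes describe a state, not a change. A patient who arrives with a stable high creatinine, or already on maintenance dialysis, satisfies the list on admission. A patient with long-standing symptomatic heart failure can satisfy every heart-failure item at once.

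Section 2.5 relates immune cell subsets to prognosis by two-group tests and by ROC curves with Youden-optimal cut-offs. Patients whose event predates the heatstroke weaken a marker that does track heatstroke injury. If the marker happens to differ in chronic disease, they can also create an association that reflects comorbidity; the documents do not say whether it does. With about 40 heatstroke patients, events will be few and each misclassified one carries weight.

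**Working it through.** **Inputs.** Heatstroke cohort of 40 (sections 2.1.1 and 2.3). Endpoint definitions from section 2.2, exclusions from Table 1, recorded items from section 2.4 and Table 2. The documents give no event rate for these endpoints and no prevalence of chronic disease, so there is no figure of the plan's own to reproduce.

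**Step 1: the three organs side by side.**

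| Organ | Does a criterion require something new? | Rule for earlier disease | Named baseline item |
|---|---|---|---|
| Lung | No | Yes | Asthma, chronic obstructive pulmonary disease |
| Kidney | Only the 3-times-baseline route | None | None |
| Heart | No | None | Cardiovascular disease (broad) |

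**Step 2: apply the written list to test cases.**

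- Stable creatinine of 4.5 mg/dL: the ratio to baseline is 4.5/4.5 = 1, so the 3-times route is not met. But 4.5 ≥ 4.0, and *or* makes that sufficient.
- Maintenance dialysis: the renal replacement route can be met with no new injury. The urine-output routes name no prior state either.
- Chronic heart failure with breathlessness, signs, an abnormal ECG, LVEF ≤ 40% and raised BNP: all items are met together, none of them new. A low LVEF without the others does not meet the list.

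**Step 3: size, under assumed figures.** Let k of the 40 patients enter already meeting a renal criterion, with k from 0 to 4 (0–10%, assumed), and let 6 others have true new events (assumed).

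Counted incidence = (6 + k)/40. Pre-existing share s = k/(6 + k).

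| k | Counted incidence | Pre-existing share of counted events |
|---|---|---|
| 0 | 6/40 = 15.0% | 0/6 = 0% |
| 1 | 7/40 = 17.5% | 1/7 = 14% |
| 2 | 8/40 = 20.0% | 2/8 = 25% |
| 3 | 9/40 = 22.5% | 3/9 = 33% |
| 4 | 10/40 = 25.0% | 4/10 = 40% |

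**Step 4: how likely is k ≥ 1?** If each patient has probability p of entering with such disease, P(k ≥ 1) = 1 − (1 − p)^40. For p = 0, 1%, 2%, 5% and 10% this is 0, 33%, 55%, 87% and 98.5%.

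**Step 5: effect on an ROC curve.** If the marker is unrelated to chronic disease, the pre-existing cases discriminate at 0.5, so apparent AUC = (1 − s) × true AUC + s × 0.5. With an assumed true AUC of 0.80 this is 0.80 − 0.30s: 0.80 at s = 0, 0.76 at s = 1/7 and 0.68 at s = 4/10.

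**The case against.** The strongest reply is that the endpoint is called acute, is defined as stage 3 acute kidney injury under KDIGO, and is reported as an incidence. An assessor could reject a dialysis patient with no new injury on the label alone. That stands to this extent: a reader might infer that chronic disease **is** counted, and the text supports only that it **can be**. The label does not close the gap, because the section spells out operative criteria and gives no rule for setting chronic cases aside, while for the lung it does give one.

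Three further inferences are tempting and not supported.

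- *LVEF ≤ 40%, or an ECG finding, is enough for a heart-failure event.* It is not. These are items in an *and* list, and the ECG findings are only examples.
- *Patients with earlier disease cannot be identified later.* This goes too far. Cardiovascular disease is recorded, and baseline laboratory results may include creatinine. The comorbidity list is also a journal summary, and the case report form is not shown. What can be said is that chronic kidney disease is not a named item, and that a value from Visit 1, within 24 hours of admission, may already reflect the heatstroke and so cannot by itself separate chronic from acute disease. Cardiovascular disease is a broad heading that does not single out chronic heart failure.
- *The study's main conclusions are at risk.* They are not. These are secondary endpoints of an exploratory study; 30-day mortality and the comparison of heatstroke with the other cohorts do not use them.

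The size is also open to challenge. Both the number of affected patients and the number of true events are assumptions, and the effect is nil if no such patient is enrolled.

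**Conclusion.** The point holds in a limited form. Section 2.2 treats earlier disease for the lung and not for the kidney or heart. Applied as written, two renal routes can count long-standing kidney disease as an incident heatstroke event, and the full set of heart-failure items can count symptomatic chronic heart failure. Chronic kidney disease is on neither the exclusion list nor the named comorbidity list, which makes the kidney the weaker of the two.

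For the kidney, the share of counted events that are pre-existing runs from 0 to 40%, assuming 0 to 4 affected patients in 40 and 6 true events. No corresponding figure is offered for the heart. The effect ranges from negligible to material according to a prevalence that the documents do not give. It is confined to secondary prognostic endpoints. The correction is worth making because it is cheap and the cohort is small.

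**What to change.** In section 2.2, state one rule for pre-existing disease across lung, kidney and heart, and define it by status at entry. The present lung sentence acts only on patients who go on to meet the criteria, so copying it to the other organs would remove patients according to their outcome.

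- **Renal replacement:** count it only if newly started after onset of heatstroke. Classify patients on maintenance dialysis at entry as not at risk for the renal endpoint, whatever their outcome.
- **Creatinine ≥ 4.0 mg/dL:** where a pre-admission value exists, require a rise from it. Where none exists and there is no known chronic kidney disease, keep the event and examine this in a sensitivity analysis. Do not use the lowest in-stay value as baseline: a patient who arrives above the threshold and dies before recovery would show no rise, so true events would be lost among the sickest. Say in advance how known chronic kidney disease with no earlier value is handled.
- **Heart failure:** in patients with known chronic heart failure, count only an acute worsening. Do not require an earlier echocardiogram in anyone else, since emergency admissions will often lack one.
- **Case report form:** add chronic kidney disease or maintenance dialysis, and chronic heart failure, as separate items.

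The cost is a few lines of endpoint text, two form fields, one sensitivity analysis, and slightly fewer renal and cardiac events in a small cohort.

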### Minimal sample size

2.3.

We did not calculate minimal sample size to achieve a given statistical power because this is an exploratory study (28, 29) and we are unaware of other studies with a similar design and purpose. Recent studies of the protective effects of precooling and curcumin on organ injury among patients with EHS included only 8–12 participants (30, 31). A study that examined immune cell dynamics during EHS was able to obtain statistically significant results using only 11 patients (32). Therefore, to differentiate the immune profiles, we aim to enroll at least 40 subjects in each of the four cohorts.

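### Section 2.2 excludes patients with prior lung disease only if they develop respiratory failure, so incidence of that endpoint is understated and some of its marker associations can be biased

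*Protocol article*

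**What the plan says.** Section 2.2 (Endpoints) sets the prognostic endpoints for heatstroke patients: "the primary endpoint is all-cause mortality within 30 days", and then "The secondary endpoints include incidence of the organ injury events within 30 days", with respiratory failure as one of four organ injuries. Respiratory failure is hypercapnic acidosis, "or as PaO_2_/FiO_2_ < 200 based on invasive or non-invasive ventilation or arterial blood gas analysis (26, 27) within 30 days".

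The rule at issue closes that paragraph. Its trigger is "If patients with concomitant pulmonary diseases prior to admission meet above diagnostic criteria"; its consequence is that "the patient will not be considered to have lung injury caused by heatstroke and will be excluded". The sentence does not say whether the exclusion is from this endpoint or from the study. No similar rule is attached to mortality or to the other three organ injuries.

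Table 1 (section 2.1.1) has no exclusion for lung disease. It lists pregnancy, immune disease, "Comorbid with malignant tumor and hematological diseases", transplantation and immunosuppressive therapy. Patients with lung disease are therefore enrolled, and section 2.4 records it at baseline: "Comorbidities include cardiovascular disease, hypertension, asthma, chronic obstructive pulmonary disease". Section 2.3 gives the cohort size: "we aim to enroll at least 40 subjects in each of the four cohorts".

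**The concern.** The trigger has two parts, prior lung disease and the event itself. The second can become known at any time up to day 30, whereas blood is drawn within 24 hours of admission (section 2.4.1). Two patients with the same baseline lung disease are thus treated differently according to outcome: the one with respiratory failure leaves, and the one without it counts as a non-event.

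The apparent aim is to count only lung injury attributable to heatstroke. The rule does not achieve this. It gives neither the incidence in all heatstroke patients nor the incidence in those free of lung disease. It also leaves an event group with no lung-disease patients, compared with a non-event group that still has them. Section 2.5 plans t-tests or Mann–Whitney tests and ROC curves with Youden cut-offs for markers against prognosis, and mentions no term for lung disease. A marker that tracks chronic lung disease could therefore look protective against respiratory failure, or look weaker than it is, because of the exclusion alone.

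**Working it through.** The article states no respiratory-failure rate and no prevalence of lung disease, so there is no figure of its own to reproduce. All rates below are assumptions. The only input from the document is the cohort of 40 (section 2.3).

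**Incidence.** Let q be the share with prior lung disease, and r0 and r1 the respiratory-failure risks without and with it.

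- Everyone counted: (1 − q)·r0 + q·r1
- Under the rule: (1 − q)·r0 / (1 − q·r1)
- All lung-disease patients left out by baseline status: r0

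The second is below the first whenever some lung-disease patient has the event and not every patient in the cohort does. It is below r0 whenever some lung-disease patient is event-free, since then 1 − q < 1 − q·r1. The direction therefore needs no assumption about the size of the rates.

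With r0 = 25% and r1 = 50%:

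| Lung disease, of 40 | Everyone counted | Under the rule | Without lung disease |
|---|---|---|---|
| 2 | (1 + 9.5)/40 = 26.3% | 9.5/39 = 24.4% | 25% |
| 4 | (2 + 9)/40 = 27.5% | 9/38 = 23.7% | 25% |
| 8 | (4 + 8)/40 = 30.0% | 8/36 = 22.2% | 25% |
| 12 | (6 + 7)/40 = 32.5% | 7/34 = 20.6% | 25% |

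Extra risk from lung disease is not needed. With r0 = r1 = 30%, the rule gives 0.285/0.985 = 28.9% at q = 5% and 0.21/0.91 = 23.1% at q = 30%.

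If the sentence instead meant that the event is not counted but the patient is kept, the 8-patient case would give 8/40 = 20%.

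**Which group changes.** In the 8-patient case, lung disease makes up 4/12 of the events before the rule and 0/8 after it. Among non-events it is 4/28 both times. The rule depletes the cases and leaves the non-events as they were.

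**Markers against respiratory failure.** AUCs from simulation (500,000 patients per scenario) with q = 20%. Respiratory-failure risk at the average marker value is 30% without and 50% with lung disease. A real marker has a log odds ratio of 0.8 per SD; a null marker has no effect within either lung-disease group.

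| Marker | Everyone counted | Under the rule | Baseline exclusion |
|---|---|---|---|
| Null, unrelated to lung disease | 0.502 | 0.502 | 0.502 |
| Real, unrelated to lung disease | 0.699 | 0.708 | 0.703 |
| Null, 1 SD higher in lung disease | 0.536 | 0.459 | 0.498 |
| Real, 1 SD higher in lung disease | 0.717 | 0.663 | 0.702 |

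For the 1 SD shift, the null marker goes from 0.523 to 0.482 at q = 10% and from 0.546 to 0.437 at q = 30%. The real marker goes from 0.711 to 0.684 and from 0.721 to 0.642.

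**Mortality, only if the exclusion is from the study.** Take q = 20%, r0 = 30%, r1 = 50%, and assume 60% die with respiratory failure and 30% without. Respiratory failure is 0.8 × 0.30 + 0.2 × 0.50 = 34%. Mortality is 0.34 × 0.6 + 0.66 × 0.3 = 40.2%. The rule removes 0.2 × 0.5 × 0.6 = 6% of the cohort as deaths, which is 2.4 of 40. Observed mortality becomes (0.402 − 0.06)/0.90 = 38.0%. The AUC for death of the real marker with a 1 SD shift moves from 0.563 to 0.543.

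**The case against.** The strongest defence is that the sponsor deliberately does not attribute these events to heatstroke, so a rate that includes them is the wrong yardstick. Against the rate in patients without lung disease, the 8-patient case gives 25% versus 22.2%, which is 9 versus 8 events in 36. Prevalence may also be low: section 2.5 describes exertional heatstroke as occurring in young people, and with 2 affected patients the gap from 25% is under one percentage point. The endpoint is one of four organ injuries, all secondary, in a study labelled exploratory. These points limit the size and the severity. They do not rescue the rule, which misses its own apparent target as well.

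Three stronger readings are tempting, and the document supports none of them.

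- A reader might infer that every marker association is biased. Markers unrelated to lung disease hardly move (0.699 to 0.708), and null ones stay at 0.50.
- A reader might infer that non-events become enriched with lung-disease patients. That group is unchanged, at 4/28 either way.
- A reader might infer that 30-day mortality is understated. The sentence concerns the cause of lung injury and sits in the respiratory-failure paragraph, study-level exclusions are in Table 1, and no such rule is attached to mortality. Removal from this endpoint only is the more natural reading. The text does not settle the matter, so the scope has to be stated, but harm to mortality cannot be asserted.

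**Conclusion.** The point holds for the respiratory-failure endpoint. The exclusion is conditional on the outcome and lowers incidence whenever a patient with prior lung disease has the event. That direction follows from the rule itself; the size cannot be obtained from the article. Under the assumed 25% and 50% risks, with 4 to 12 of 40 patients affected, the shortfall is about 4 to 12 percentage points against counting everyone and about 1 to 4 points against patients without lung disease.

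Associations with respiratory failure can be biased for markers that differ by lung-disease status, enough in the assumed 1 SD case to make a null marker look protective. Effects on mortality, the remaining endpoints and the 1:1 matched sets of section 2.1.2 arise only if the exclusion is from the study. Severity: should fix.

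**What to change.** Replace the last sentence of the respiratory-failure paragraph in section 2.2 with a rule that depends on baseline status only. There are two sound options, and one can be primary with the other as a sensitivity analysis:

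- count respiratory failure in every heatstroke patient, and stratify or adjust for prior lung disease as far as the number of events allows; or
- leave all patients with prior lung disease out of this one endpoint, whatever their outcome.

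State also that the exclusion applies to this endpoint alone, and that all patients stay in the mortality analysis and the other endpoint analyses.

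The cost is a sentence or two. Asthma and COPD are already recorded at baseline under section 2.4; if the sponsor means a wider set of pulmonary diseases, that set should be named. Under the first option, some counted events may not be purely due to heatstroke. Under the second, a few patients are lost from one secondary endpoint.
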